### Statistics and power calculation

#### Statistics

The data from the trial will be analyzed both separately for each patient category using classical statistical analyses and merged across the different patient categories and sampling time-points using computational modelling.

The data will be analyzed by classical statistical analyses i.e. descriptive statistics will be calculated for endpoints with summary statistics for continuous variables including n, means with standard deviation and medians with min/max or inter quartile ranges and summary statistics for categorical variables including n and proportions. Differences in continuous variables (including calculated delta-values) within groups between time-points will be analyzed by paired tests (t-test, Wilcoxon-signed rank test), mixed models or repeated measurements analysis (ANOVA, ANCOVA, Friedman), the latter followed by post hoc pairwise comparisons. Differences across different patient-groups or responses will be analyzed by two-sample t test or Mann-Whitney U test. Differences in categorical values will be analyzed by Chi-square tests or Fishers exact test as appropriate and McNemars test for changes over time.

The predictive value of immunologic variables or categorized immunologic variables for the endpoints will be analyzed by survival statistics including Kaplan-Meier plots and log rank test and Cox proportional hazards models. Furthermore, linear and logistic regression models will be applied to investigate the predictive value of immunologic variables for continuous and categorical endpoints. Analyses may be stratified by underlying disease/baseline patient characteristics, and odds ratios of outcomes among patients with an immunologic variable below or above a certain threshold will be estimated by logistic regression analyses adjusted for relevant covariates. The sensitivity, specificity, positive- and negative predictive value of specific immunologic variables or patterns for outcome will be calculated. *P*-values < 0.05 will be considered significant.

Furthermore, computational modelling of data applying a bioinformatics approach will be conducted by e.g. unsupervised learning to reveal patterns in the immunologic variables and profile predictive for the endpoints (data mining, clustering and/or Bayesian models, principal component analyses (PCA)).

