### Study-participants

To be eligible for the study the participant must be a minimum of 18 years of age and have a planned kidney-, heart-, lung-, liver- or pancreas-transplant and be able to provide informed consent. Study participation is strictly voluntary.

During a three-year-period we aim to include 630 SOT recipients: *n* = 270 kidney-, *n* = 90 lung-, *n* = 45 heart-, *n* = 180 liver-, and n = 45 pancreas recipients from Rigshospitalet, University of Copenhagen [1]. A study nurse is employed to ensure adequate participant enrolment and complete follow-up.

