#### Statistical power

The total number of patients planned investigated are *n* = 630 SOT recipients. We have performed power calculations to ensure adequate power:

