#### Plasma biomarkers

Several studies have reported that plasma sCD30 predicts infectious complications and acute rejection [33, 34] in kidney transplant recipients with a 64% vs. 75% 5-year graft survival in patients with high vs. low sCD30 levels [34]. To detect such likely-hood ratio with α = 0.05 and power(β) = 0.75, a total of *n* = 486 patients is required.

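### The Statistics section assigns the P < 0.05 analyses to each patient category separately, but the sCD30 power calculation (n = 486) can only be met by a test across organs, and none is clearly assigned

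*Protocol article*

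**What the plan says.** The opening sentence of the Statistics section allocates methods to data, which it describes as "analyzed both separately for each patient category using classical statistical analyses and merged across the different patient categories and sampling time-points using computational modelling". Classical methods listed after it include every named test of an immune variable against an endpoint: log-rank, Cox and logistic regression, all judged at P < 0.05. The merged branch is illustrated by "unsupervised learning to reveal patterns in the immunologic variables and profile predictive for the endpoints", with clustering, Bayesian models and principal components as examples. No test is named there as deciding.

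Two other sentences touch on groups. One reads "Differences across different patient-groups or responses will be analyzed by two-sample t test or Mann-Whitney U test". The other is optional: "Analyses may be stratified by underlying disease/baseline patient characteristics".

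The Study-participants section plans 270 kidney, 180 liver, 90 lung, 45 heart and 45 pancreas recipients. The power section argues from the total: "The total number of patients planned investigated are *n* = 630 SOT recipients. We have performed power calculations to ensure adequate power". Under Plasma biomarkers it takes a "64% vs. 75% 5-year graft survival in patients with high vs. low sCD30 levels", reported in kidney recipients, and states that 486 patients are needed at alpha 0.05 and power 0.75.

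**The concern.** The sample size is justified by a total that no single organ group reaches, while the tests are assigned to the organ groups. If the opening sentence is followed literally, a marker of moderate strength is tested five times with low power and never once with the power the article relies on.

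The second aim in the Background is to determine whether immune profiling predicts infections and rejections in transplant recipients. Five separate tests of unequal size can give five different answers. For a moderate effect that is the same in every organ, the likely pattern is significant in the larger groups and non-significant in the smaller ones, which can be mistaken for biology. The article plans to carry its results into trials of personalised immunosuppression, so a misleading organ pattern could influence their design.

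**Working it through.** **Inputs.** From the article: group sizes 270, 180, 90, 45 and 45 (sum 630); alpha 0.05; 64% vs 75% graft survival, so event risks p1 = 0.36 and p2 = 0.25 with mean 0.305; power 0.75; stated total 486. Assumed: two-sided tests, the same effect in every organ, and half of each group marker-high (25% as a check).

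**1. The article's own figure.** Two proportions, pooled variance, no continuity correction:

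n per group = [1.960 × √(2 × 0.305 × 0.695) + 0.6745 × √(0.36 × 0.64 + 0.25 × 0.75)]² / 0.11²
= [1.960 × 0.6511 + 0.6745 × 0.6465]² / 0.0121 = 242.3, rounded up to 243, or 486 in total.

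This reproduces the stated number. A one-sided test would need 376. Both exceed 270, the largest organ group.

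**2. Power of the organ-separate tests.** Power = Φ[(0.11 − 1.960 × s0) / s1], where s0 = √(0.305 × 0.695 × 4/N) and s1 = √((0.36 × 0.64 + 0.25 × 0.75) × 2/N).

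| Group | N | s0 | s1 | z | Power |
|---|---|---|---|---|---|
| Kidney | 270 | 0.0560 | 0.0556 | 0.00 | 50% |
| Liver | 180 | 0.0686 | 0.0681 | −0.36 | 36% |
| Lung | 90 | 0.0971 | 0.0964 | −0.83 | 20% |
| Heart, pancreas (each) | 45 | 0.1373 | 0.1363 | −1.17 | 12% |
| All recipients | 630 | 0.0367 | 0.0364 | 1.05 | 85% |

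An organ-stratified Cochran-Mantel-Haenszel test simulated on all 630 (40,000 runs) also gives 85%. With a 25/75 marker split, the organ powers are 42%, 31%, 18%, 12% and 12%, against 75% for all 630.

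**3. How often the organs disagree although the effect is common.** The groups contain different patients, so the probabilities multiply.

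- All five significant: 0.501 × 0.359 × 0.203 × 0.122² = 0.0005.
- None significant: 0.499 × 0.641 × 0.797 × 0.878² = 0.197.
- Some but not all: 1 − 0.0005 − 0.197 = 0.80 (0.74 with the 25/75 split).

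Other effects: an assumed 45% vs 25% gives a mixed picture in 97% of trials, and an assumed odds ratio of 2 on a 20% risk gives 93%. The very large effect in the TruCulture section (58% vs 6.6%) gives only about 3–4% with an even split and 11% with a 25/75 split.

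**4. False positives if any single organ counts.** 1 − 0.95⁵ = 22.6% per marker and endpoint (22.3% simulated). The single organ-stratified test stays at 5.1%.

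**The case against.** The strongest reply is that the opening sentence is introductory and not exclusive. The detailed paragraphs do not confine Cox, log-rank or logistic models to one organ. Tests across patient groups cannot be run inside one category. Optional stratification and covariate adjustment would fit a pooled model, and the figure of 486 itself suggests that a comparison across organs was in mind. Patient category is undefined, so equating it with organ is an inference, though a natural one. All this stands against a reader who infers that the plan forbids pooled tests. It does not remove the conflict: the one sentence that allocates methods points away from the test the power section needs. The cross-group tests compare levels of continuous variables, not marker-endpoint associations.

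A statistical analysis plan, not shown, may name a deciding contrast or an interaction test. Their absence from the article is therefore not the point. The point is a split that the article states and that its own figures contradict.

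A reader might also take 22.6% as the plan's error rate. The article nowhere says that significance in any one organ makes a marker predictive, and each organ-specific statement keeps its own 5%. The figure applies only if results are used that way.

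A reader might further infer that a common effect will always look organ-specific. That fails for the TruCulture effect, and for 36% vs 25% about 20–26% of trials would show no significant organ at all. Taken at face value, the other two stated sizes (28 and 24) fit inside even the smallest group of 45, so the conflict is with the sCD30 calculation.

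Finally, organ-specific analysis has a rationale: the Background cites rejection rates from 24% to 60% by organ.

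**Conclusion.** The concern holds as an inconsistency between the stated analysis split and the stated power. The sCD30 calculation needs 486 patients; the largest organ group has 270 and about 50% power for that effect. That shortfall applies even in kidney, the organ in which the article says the effect was reported. Testing across organs restores about 85% if the effect is common to all organs, half the recipients are marker-high and all 630 have the marker measured. The last condition is uncertain, because the article allows plasma biomarkers and flow cytometry to be limited to between 100 and 630 participants; smaller numbers lower every power figure here.

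For moderate common effects, mixed verdicts between organs would be usual (about 74–97% over the scenarios above) and would reflect group size. The documents do not support the stronger claims that pooled tests are excluded, that the plan's error rate is 22.6%, or that every real effect will look organ-specific.

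**What to change.** Amend the first sentence of the Statistics section. For each marker and primary endpoint, the main classical analysis is one model on all recipients with the marker measured: Cox stratified by organ, or logistic regression with organ terms. A marker-by-organ interaction test and organ-specific estimates with 95% confidence intervals follow as secondary results. Computational modelling remains as planned. If organ-separate tests are to stay the main analysis, restate the power section for the organ group sizes instead. A Bonferroni level of 0.05/5 = 0.01 would not rescue that option for the sCD30 effect: power falls to 27% in kidney, 16% in liver, 7% in lung and 4% each in heart and pancreas.

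The cost is a change of wording and one extra model per marker and endpoint, on data already being collected. The downside is real: a common-effect test is less efficient for a marker that acts in one organ only, and the interaction test detects a kidney-only or liver-only odds ratio of 2 (20% risk otherwise) in only about 18–22% of trials. Organ-specific estimates should therefore still be reported, and a non-significant interaction should not be read as proof of a common effect.

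### Covariate-adjusted logistic regression within organ groups of 45 gives exaggerated and unstable odds ratios under standard maximum likelihood; the small-group models need a penalised fit

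*Protocol article*

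**What the plan says.** The Statistics section opens with how the study data are to be handled: "analyzed both separately for each patient category using classical statistical analyses". The pooled data, by contrast, are to be "merged across the different patient categories and sampling time-points using computational modelling". Pooling across organs is thus attached to the computational work, and organ-specific analysis to the classical methods.

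One of the classical analyses concerns the odds of an outcome in "patients with an immunologic variable below or above a certain threshold". The article states that these odds ratios "will be estimated by logistic regression analyses adjusted for relevant covariates". It gives no penalised or exact method, no covariate limit and no minimum number of events. The same paragraph adds: "Analyses may be stratified by underlying disease/baseline patient characteristics". That would make the groups smaller still.

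Under Study-participants the planned numbers are 270 kidney, 180 liver, 90 lung, 45 heart and "n = 45 pancreas recipients from Rigshospitalet". The sections on immune phenotype and circulating plasma biomarkers allow those measurements in as few as 100 of the 630 participants, depending on funding.

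**The concern.** Maximum-likelihood log odds ratios are biased away from zero when there are few events per parameter. With very few events, some fits have no finite estimate (separation). A marker term plus several covariates in 45 patients is in that range, and a kidney model with 270 patients is not. On average, therefore, the same true effect would appear larger in heart and pancreas than in kidney, and the small-group estimates would include some extreme values. At stake is the size of the reported organ-specific associations, and any comparison of point estimates between organs.

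**Working it through.** **The plan's own figures.** The article gives no figure for the adjusted logistic model. The nearest are unadjusted two-group sample sizes. With two-sided 5%, 1:1 groups and n per group = [1.96·√(2·p̄·q̄) + z_β·√(p₁q₁ + p₂q₂)]² / (p₁ − p₂)²:

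- 58% vs 6.6%, 80% power: 11.7, so 12 per group and 24 in total (stated 24).
- 64% vs 75%, 75% power: 242.3, so 243 per group and 486 in total (stated 486).

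Both reproduce, but neither bears on a covariate-adjusted model.

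**Events per parameter.** Take n × min(p, 1 − p) / (k + 1), with k covariates plus the marker. For n = 45:

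- 56% risk (heart rejection, Background): 45 × 0.44 = 19.8 in the smaller outcome class. This gives 9.9 with one covariate, 6.6 with two and 3.3 with five.
- 28% risk (assumed): 12.6 events, giving 6.3, 4.2 and 2.1.
- 10% risk (assumed; the article gives no rate for bloodstream infection, CMV infection or pneumonia): 4.5 events, giving 2.2, 1.5 and 0.8.

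No 45-patient model reaches 10, even with one covariate.

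**Simulation, n = 45, true odds ratio 3.** Assumptions: marker split 50/50, standard-normal covariates with log odds ratio 0.4 each, 3,000 replicates. The typical value is exp(mean log odds ratio) over finite estimates.

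| Risk | Covariates | ML typical | ML above 10 | ML not finite | Firth typical | Firth above 10 |
|---|---|---|---|---|---|---|
| 30% | 1 | 3.34 | 8.8% | 1.2% | 3.02 | 5.3% |
| 30% | 3 | 3.69 | 13.6% | 1.1% | 3.04 | 7.7% |
| 30% | 5 | 4.12 | 18.5% | 1.1% | 2.99 | 7.7% |
| 56% | 1 | 3.30 | 6.6% | 0% | 3.00 | 3.6% |
| 56% | 3 | 3.58 | 10.9% | 0% | 3.00 | 5.3% |
| 56% | 5 | 4.08 | 17.0% | 0.1% | 3.07 | 6.9% |
| 10% | 1 | 2.27 | – | 31% | 2.72 | – |
| 10% | 5 | 3.00 | – | 39% | 2.71 | – |

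At 10% risk the finite ML estimates do not look inflated, because the infinite ones have dropped out. The fault there is the missing estimates.

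**True odds ratio 2.5, n = 45.** ML gives about 2.6 to 2.9 with one or two covariates and about 3.3 with five, at 28% and at 56% risk. Firth gives 2.4 to 2.6, with a root mean squared error on the log scale 12 to 31% lower at these risks. At 10% risk about 28% of ML fits are not finite. Separate runs differ in the second digit. With a standard deviation of 0.89 and 2,000 replicates, the simulation error of the mean log odds ratio is 0.89/√2000 = 0.02.

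**True odds ratio 1.** At 30 to 56% risk the typical ML value is 0.99 to 1.02, so there is no shift.

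**Larger groups, true odds ratio 3, 24 to 56% risk.** ML gives 3.2 to 3.5 at n = 90, 3.05 to 3.23 at n = 180 and 3.04 to 3.13 at n = 270.

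**Subset measurement.** If 100 patients were measured in proportion to the planned enrolment (an assumption), the organ numbers would be 100 × 270/630 ≈ 43 kidney, 29 liver, 14 lung, 7 heart and 7 pancreas. Every organ group would then be below 45.

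**The case against.** The strongest reply is that the article says only logistic regression. It does not say maximum likelihood, and it fixes no number of covariates. Firth regression is also logistic regression, and the estimator could be named in an analysis plan that is not shown. It is also arguable how strictly the per-organ sentence governs the odds-ratio models. Stratification is worded as optional, differences across patient groups are also tested classically, and the 486 required for plasma biomarkers exceeds any single organ group. These points limit the confidence. They do not remove the point: the opening sentence assigns classical analyses to each category, the 45-patient groups are fixed, and the unqualified term ordinarily means maximum likelihood.

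Several stronger readings are tempting and are not supported:

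- **False positives.** A reader might infer spurious significance. Wald 95% coverage was 94 to 97%, and false-positive rates were 4.6% and 4.8% with two and five covariates. The least favourable repeat run (56% risk, five covariates, 2,000 replicates) gave 6.7%. Inference is close to nominal.
- **Heart and pancreas will look worse than kidney in this study.** With two covariates at 28% risk the bias is ln(2.89) − ln(2.5) ≈ 0.14, against a standard deviation of 0.89. Chance dominates in any one study. The bias is an average tendency.
- **An overstatement of a third or more.** That needs about five covariates, which the article does not propose.
- **Direct harm to the later randomised trial.** The article carries prediction models forward, built from classical and computational work together. It does not name heart- or pancreas-specific odds ratios as inputs.
- **The same for Cox models.** No Cox simulation was run, so nothing is claimed.

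**Conclusion.** The point holds in a limited form. Followed as written with the standard estimator, the per-organ adjusted models for heart and pancreas overstate a real effect on average: by 4 to 16% with one or two covariates (2.6 to 2.9 against 2.5) and by about 32% with five (3.3 against 2.5). For endpoints near 10% risk, roughly three fits in ten have no finite estimate. The size rests on the assumed covariate number, event risk, marker split and covariate strength. The conclusion is much the same at 28% and 56% risk.

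At the event risks examined, kidney and liver at full size are little affected. Lung is intermediate and depends on the covariate list. The same weakness would reach every organ for phenotyping and plasma markers if only about 100 patients were measured. This is a modest, inexpensive improvement to the precision and credibility of small-group estimates. It does not threaten the validity of the study's tests.

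**What to change.** Add to the analysis plan: for the heart and pancreas models, and for any other organ or subset model with fewer than about 10 events (smaller outcome class) per parameter, adjusted odds ratios are estimated by Firth-penalised logistic regression with profile-likelihood intervals, and adjustment is limited to one or two pre-named covariates. Kidney and liver models at full size stay as they are. Only a rare endpoint or a long covariate list would bring one of them under the count.

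Limiting covariates alone removes much of the average bias but does not deal with missing estimates for rare endpoints, so both parts are needed. A single model across organs with organ and marker-by-organ terms is a reasonable alternative.

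The cost is one or two sentences and a standard software option. Small-organ odds ratios will move closer to 1. At 10% risk Firth itself falls slightly short (about 2.7 to 2.8 for a true 3). Firth also raised mean predicted risk by 1.5 to 2.2 percentage points at n = 45 and 28% risk, so an intercept correction is needed if these models are used for prediction.

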Whole blood is transferred to five different tubes. Four of the tubes are coated with stimulants, mimicking a fungal infection (heat killed *Candida albicans*), bacterial infection (LPS) and viral infection (Resiquimod R848 and Poly I:C). The fifth tube does not contain stimulant and serves as a negative control. This tube allows for assessment of in vivo activation. The whole blood is incubated for 22 h at 37 °C before the supernatant is harvested for analysis of biomarkers, the cells are stabilized with Trizol for analysis of mRNA. TLR: Toll-like-receptors.

Anticoagulated whole blood is transferred to individual TruCulture® tubes 60 min after blood sampling. After 22 h incubation at 37 °C, the TruCulture® supernatant is harvested, aliquoted, and stored at − 80 °C for later thawing and bulk analysis of soluble immune activation products (cytokines, chemokines, soluble receptors etc.) by Luminex®, Meso Scale Discovery® (MSD®) or ELISA.

The mRNA in the TruCulture® cell pellet is stabilized by Trizol and stored at − 80 °C for later bulk analysis of mRNA expression level of stimulated immune proteins. The technique applied for mRNA quality control and expression analysis will be commercially available and one that the laboratory is familiar with and applies at the time for mRNA expression analysis e.g. the multiplex assay nCounter GX Human Immunology Kit (NanoString Technologies) covering 511 human genes (shared among 24 immunology-related gene networks) known to be differentially expressed in immunology.

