#### Flow cytometry

Fernandez-Ruiz et al. [32] have found that a low NK-cell count (< 0.050 × 10^3^ cells/μL) at month one post liver-transplantation was associated with a greater risk of opportunistic infections at month one to six post transplantation. To detect such likely-hood ratio with α = 0.05 and power(β) = 0.80 for the incidence rate of 0,09 OI/1000 days vs. 0,58 OI/1000 days a total of *n* = 28 SOT recipients is required.

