#### TruCulture®

To our knowledge, TruCulture® has not been used to investigate SOT recipients. In oncologic patients undergoing neoadjuvant radio- and/or chemotherapy before surgery, low IL-12 production in LPS stimulated whole blood cultures predicts increased sepsis-related mortality (58% vs. 6.6%) [35]. To detect such likely-hood ratio with α = 0.05 and power(β) = 0.80, a total of *n* = 24 patients is required.

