The TruCulture® is a novel functional immune assay that will provide complex information about the immune function [24]. TruCulture® was developed at the Institut Pasteur, France, with the purpose to be incorporated in the *Milieu Intérieur*-project, which is a large-scale study of 1000 healthy French adults [37]. In the ImmuneMo:SOT study the TruCulture® consists of four carefully chosen stimuli, mimicking fungal, bacterial and viral presence, acting through different TLR pathways. Furthermore, we have chosen 8 cytokines (TNF-α, IL-1β, IL-6, IL-8/CXCL8, IL-10, IL-12p40, IL-17A, IFN-γ) as readout providing a broad and representative image of the immune function. We expect this functional assay to provide much needed information about the global immune function of the SOT-recipients.

This ImmuneMo:SOT study is a non-interventional, observational, prospective study. The primary aim is to generate new knowledge about the immune function in SOT recipients and to link this information to risk of infections and rejections. When combining classical statistics and computational bio-informatic approaches to the data generated, it is expected that the study will be able to generate prediction models that can be used to design a treatment program using personalized medicine. Other ImmuneMo studies including other groups of patients undergoing immune modulating interventions are underway (patients treated with biological treatments, hematopoietic stem cell transplantation recipients, HIV-infected patients, patients with cancer, and patients with severe bacterial infections). Furthermore, a collaboration with Milieu Intérieur will provide the boundaries for the immune function in healthy individuals.

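### P < 0.05 is the only significance criterion for the classical marker-endpoint tests; applied readout by readout to TruCulture alone, it would yield about 13 to 16 false positives if all are null

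*Protocol article*

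**What the plan says.** The Statistics section of the protocol article describes two strands of analysis.

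- **Classical analyses**, run separately for each patient category. They include paired and repeated-measures tests, post hoc pairwise comparisons, two-sample comparisons, log-rank tests, Cox models, linear and logistic regression, and odds ratios above or below an unspecified threshold. The paragraph on predictive value ends with the only decision rule given: P-values below "0.05 will be considered significant".
- **Computational modelling** on data merged across categories and time points. It is described in a separate paragraph after that rule.

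The Discussion presents eight cytokines "as readout providing a broad and representative image of the immune function", and the Immune function section describes five tubes, four stimulated and one negative control. For mRNA, that section gives as an example a kit "covering 511 human genes".

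Each of the three power calculations concerns one marker at alpha 0.05. The TruCulture calculation uses a finding that low IL-12 production "predicts increased sepsis-related mortality (58% vs. 6.6"%).

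**The concern.** One fixed threshold is stated for a screen of many markers, at several times, against more than one endpoint. On average, 5% of the tests of markers that predict nothing will still be called significant. The article gives the reader no way to tell those from the true ones: it sets no error rate across the screen, asks for no count of tests, and does not call the tests exploratory.

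This matters because of the study's purpose. The Background says that many candidate markers have been suggested and none has proved reliable. The article expects the results to contribute to prediction models and, if the study succeeds, to later randomised trials of personalised immunosuppression. A list of significant markers with an unknown and possibly large false share is a poor starting point for either.

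**Working it through.** **1. The plan's own figures.** The formula is the usual sample size for two proportions: two-sided alpha 0.05, equal groups, pooled variance under the null, no continuity correction. The sidedness and the equal split are inferred because they reproduce the stated totals.

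| Calculation | Inputs | Per group | Total | Stated |
|---|---|---|---|---|
| TruCulture | 58% vs 6.6%, power 0.80 | 12 | 24 | 24 |
| Plasma biomarkers | 64% vs 75%, power 0.75 | 243 | 486 | 486 |
| Flow cytometry | 0.09 vs 0.58 entered as proportions, power 0.80 | 14 | 28 | 28 |

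All three reproduce, and each covers a single comparison at 0.05. None allows for a screen. (The flow cytometry figures are rates per 1000 days in the article. That they reproduce only as proportions is a separate matter.)

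**2. Number of tests, TruCulture cytokines only.** Inputs:

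- 8 cytokines (Table 1, Discussion).
- 4 stimulated tubes, or 5 with the negative control (Table 2).
- 4 usable times: pre-transplant, 7–14 days, 3 months and 6 months. The 12- and 24-month samples come too late to predict a 1-year endpoint.
- 2 primary endpoints: infection and graft rejection within 1 year.
- 5 organ groups (Study-participants), if patient category means organ type.

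Expected false positives if every test is null = 0.05 × number of tests. Correlation between tests does not alter this expectation.

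| Count | Tests | Expected false positives |
|---|---|---|
| 8 × 4 × 4 × 2 | 256 | 12.8 |
| 8 × 5 × 4 × 2 | 320 | 16 |
| 320 × 5 organ groups | 1,600 | 80 |

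**3. Chance of at least one false positive.** Take 8 × 5 = 40 null readouts at one time and for one endpoint. If independent, the chance is 1 − 0.95^40 = 87%. The article gives no correlation between readouts, so a range of common correlations is shown:

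| Assumed correlation | 0 | 0.2 | 0.4 | 0.6 | 0.8 |
|---|---|---|---|---|---|
| P(at least one P < 0.05) | 87% | 81% | 66% | 47% | 28% |

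The expected number stays at 40 × 0.05 = 2 throughout. With higher correlation the false positives arrive in clusters.

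**4. Share of significant markers that are false.** If a fraction π of markers truly predicts and power is 0.80 (assumed):

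false share = 0.05(1 − π) / [0.05(1 − π) + 0.80π]

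| π | 1% | 5% | 10% | 20% |
|---|---|---|---|---|
| False share | 86% | 54% | 36% | 20% |

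For π = 5%: 0.0475 / (0.0475 + 0.040) = 54%.

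**5. What the fix would require.** With the 320 tests split by endpoint, each Benjamini-Hochberg family has 160 tests. The k-th smallest P-value is compared with 0.05 × k/160, so a lone finding needs P ≤ 0.05/160 = 0.00031, while a tenth finding needs only 0.05 × 10/160 = 0.0031. With five organ groups the family is 800, and a lone finding needs 0.05/800 = 0.00006.

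**The case against.** The strongest reply is that this is a condensed article. Multiplicity control is commonly left to a statistical analysis plan, the study is observational and meant to generate knowledge, and the sentence is a conventional one that does not rule out adjusted P-values. Part of this stands. The absence of a named main test or of a defined testing family is not a fault here, and unadjusted P-values would be defensible if labelled exploratory. But the article does more than stay silent: it states a criterion for calling a result significant, attaches it to analyses of predictive value, and gives no such label.

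The test counts are also inferred. The article does not say that every cytokine, tube and time will be tested singly. The control tube is there to assess in vivo activation, and mixed or Cox models could combine times. This is fair, and it is why the count is conditional and given as 256 to 320.

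Four stronger readings are tempting, and the article does not support them:

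- **Thousands of gene tests.** One might compute 511 × 5 tubes = 2,555 tests and about 128 false positives per time and endpoint. The kit is only an example, and gene-by-gene testing at 0.05 is nowhere stated. The count applies only if that kit is used and genes are tested singly.
- **Most of the markers found will be false.** That depends on the unknown share of true predictors; the table in the working runs from 20% to 86%.
- **P < 0.05 is the entry rule for the prediction models.** No section says so. The Discussion derives the models from classical and computational approaches together, and the later trial is conditional on success.
- **A short confirmatory list of markers is needed.** That would be a reasonable design choice, but nothing in the article requires it.

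**Conclusion.** The point holds for the classical analyses of predictive value. Their only stated criterion is a flat 0.05, with neither multiplicity control nor an exploratory label. On the article's own inputs, with each TruCulture readout tested singly at four times for two endpoints, this means 256 to 320 tests and about 13 to 16 false positives if all are null. It becomes 1,600 tests and about 80 if repeated in five organ groups. These are counts under a complete null, not forecasts. The false share among significant markers rests on the assumed 80% power and on an unknown prevalence of true predictors. The data collected are unaffected; what needs changing is the decision rule. An unseen analysis plan may already replace it, in which case the article's sentence should be read with that plan.

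**What to change.** Replace the flat rule for tests of association between markers and endpoints:

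- Declare findings by Benjamini-Hochberg at a 5% false discovery rate within each assay and endpoint, with the family spanning readouts, sampling times and patient categories.
- Report the number of tests in each family.
- Label any unadjusted P-value exploratory.
- Describe the three calculations under Statistical power as single-marker calculations at alpha 0.05, so that they are not read as the power of the whole screen.

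The cost is that fewer markers will be called significant, and weak single-marker effects will be harder to declare than the power statements suggest. No extra patients, samples or assays are needed, and the planned 630 stands. Strict Bonferroni is not proposed. For 320 tests it would raise the 64% vs 75% plasma calculation from 486 to 1,390 patients and cut its power at 630 (equal groups) from 85% to 22%. False discovery rate control is less severe and suits a search for markers better.
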